### MRI

Patients will be positioned feet first-supine and both feet are placed simultaneously in the dorsal part of the head coil then will be examined in a 3.0-T horizontal magnet (Discovery MR750, GE Medical System, Milwaukee, WI). For morphological evaluation of the Achilles tendon, three-dimensional fat-saturated proton-density-weighted turbo-spin echo (PDTSE) will be used. Other parameters were set as follows: repetition time (TR)=202.1 ms, field of view (FOV)=140 mm× 140 mm, slice thickness (ST) = 2 mm. Four echo time images (TE=0.032, 7.5, 20.5, and 28 ms) will be obtained. T2* value of Achilles tendon insertion region is calculated by fitting the acquired signal at different echo time to a single exponential decay model.

### Primary outcome

#### Victorian Institute of Sports Assessment Achilles (VISA-A) score

The VISA-A score is a validated questionnaire for Achilles tendinopathy and contains 8 questions assessing physical activity and pain (0, no activity/maximum pain; 100, maximum activity/no pain) [34]. And it is adapted to the local language. The Chinese version has been used in clinical trials [37, 38], proving its validity (Additional file 1).

### Secondary outcome

MRI: UTE-T2* valueThe MRI UTE-T2* has been reported to show significant differences between Achilles tendinopathy and normal tendon [27–29]. Thus, the morphological information of the tendon after treatment could be monitored.Foot and Ankle Outcome Score (FAOS) scaleVisual analog scale (VAS)Tegner ScoreComplications

### Data collection

All relevant data will be collected by research fellows who are blinded to the treatment procedures and recorded in specially designed case report files. The patients will be identified by an assigned number. At the completion of the study, all identifiable data will be destroyed. The patients are informed, both verbally and in writing, that data are stored and analyzed in a computer, that the patient’s anonymity is preserved, and that the data protection legislation is adhered to.

### Adverse event management

Achilles tendon rupture, skin infections, nerve damage, and restricted ankle motion are presumably complications of both the percutaneous radiofrequency coblation and the ESWT treatment, therefore the number of complications will be registered and will be treated accordingly. Furthermore, an adverse event is defined as any unintended, unfavorable finding, symptom, or disease that occurs, whether it is considered to be related to the study or not. Adverse events will be recorded. Serious adverse events (SAEs) is defined as an event or reaction which will cause death, life-threatening situations, hospitalization or prolongation of existing hospitalization, or permanent or severe disability. SAEs will be reported to the ethics committee within 24 h.

### End of trial

The end of the trial will be defined as the collection of 2 years of outcome data from the last participant.

### Statistical analysis

All continuous data from primary and secondary outcome measurements will be summarized by descriptive statistics with the number of observations (*n*), mean, SD, minimum, median and maximum. Uncontinuous data such as co-morbidities concomitant injuries will be summarized by descriptive statistics with the number of observations, calculating the incidence separately and analyzing whether it is associated with prognosis. The primary point for analyses of efficacy will be 6 months after surgery, then 1 year and 2 years. A statistical software program (SPSS for Windows, version 23.0; SPSS Inc, Chicago, IL) will be used for statistical analysis in this study. Group comparison will be statistically analyzed by either Student’s *t* test or Mann-Whitney *U* test, depending on whether the data is normally distributed. The significance level will be set at a *p* value <0.05.

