**Methods:**

The study is a randomized, controlled trial with patients allocated in a 1:1 ratio to one of two parallel groups. Patients with insertional Achilles tendinopathy who are not satisfied with the effect of conservative treatment will be screened. A minimum of 38 patients will be enrolled after deciding to participate in the trial on an informed basis. Then the intervention group and the control group perform radial ESWT and sham-ESWT respectively at 6 months after percutaneous radiofrequency coblation. The primary outcome will be the Victorian Institute of Sports Assessment Achilles (VISA-A) Score. Secondary outcome measures will be Foot and Ankle Outcome Score (FAOS) scale, visual analog scale (VAS), Tegner Score, and MRI ultra-short echo time (UTE) T2* value. The assessments will occur in 6 months, 1 year, and 2 years, post-operatively. The differences between the 2 groups will be conducted as intention-to-treat basis.

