### Sample size

The primary outcome of this study is the VISA-A score. McCormack J et al. [32] have identified the minimum clinically important difference (MCID) of 6.5 points for the VISA-A. The study of Wei M et al. [33] indicates an expected standard deviation (SD) of 6.9 points. We have referred to the sample size calculation method of Kvalvaag E et al. [34]. To detect a difference in results between the radical ESWT and the sham-ESWT participants at a level of 5% significance and the most likely scenario for 80% power, 15 patients per group will be needed. Assuming a margin of 20% loss of primary outcome data, we propose to recruit a minimum of 38 patients in total.

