### Procedures

A patient is considered to be included in the protocol if he/she meets all of the inclusion criteria and none of the exclusion criteria. Then the patient will be verbally informed of the study and given the opportunity to decide whether he/she wants to participate in the trial on an informed basis without any pressure. Then a written informed consent will be obtained from each participant. Once included, the VISA-A Score, MRI UTE T2* value, FAOS Score, VAS Score, and Tenger Score will be assessed. Within 1 week after being enrolled, the percutaneous radiofrequency coblation will be performed by an experienced surgeon. After the surgery, each patient will randomly take an unmarked, opaque, sealed envelope containing a piece of paper with a unique number from 1 to 38. Then the numbers will be divided into two sets via computing software (https://www.randomizer.org/). All patients respectively entered the intervention group and the placebo group according to their own numbers. Patients of the intervention group will receive ESWT at 6 months post-operatively. At the same time, the patients of the placebo group will also experience sham ESWT’s procedure. Either the radial ESWT or sham ESWT will be administered 4 times at weekly intervals. In all, the treatment protocols for the two groups are similar except for the intervention: radial ESWT. All the outcome measurements will be assessed again at 6 months, 1 year, and 2 years after the surgical procedure.

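### The primary efficacy time point, 6 months after surgery, coincides with the nominal start of ESWT or sham, about 3 weeks before the randomised course ends

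*Protocol article*

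**What the plan says.** All statements are in the protocol article.

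- **Primary time point** (Statistical analysis): "The primary point for analyses of efficacy will be 6 months after surgery, then 1 year and 2 years".
- **Start of randomised treatment** (Procedures): "Patients of the intervention group will receive ESWT at 6 months post-operatively". For the sham arm: "At the same time, the patients of the placebo group will also experience sham ESWT’s procedure". The Methods paragraph of the abstract agrees, saying that the groups "perform radial ESWT and sham-ESWT respectively at 6 months after percutaneous radiofrequency coblation".
- **Length of the course** (Procedures, repeated under Extracorporeal shockwave therapy): "Either the radial ESWT or sham ESWT will be administered 4 times at weekly intervals".
- **Origin of the visit times** (Procedures): "All the outcome measurements will be assessed again at 6 months, 1 year, and 2 years after the surgical procedure".
- **What separates the arms** (Procedures): "In all, the treatment protocols for the two groups are similar except for the intervention: radial ESWT".
- **Primary outcome** (Sample size): "The primary outcome of this study is the VISA-A score". That section uses a difference of 6.5 points, an SD of 6.9, 5% significance and 80% power. It arrives at 15 per group, or 38 in total after 20% loss. It names no time point.

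**The concern.** The trial asks whether adding ESWT to coblation improves the result. A primary comparison can answer that only if it is made after the arms have been treated differently. Up to month 6 both arms have had coblation and the same rehabilitation, and differ only in their allocation. A primary analysis at month 6 therefore contrasts groups that have received none, or at most part, of the randomised treatment.

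A non-significant primary result could then be reported as showing that ESWT adds nothing, although the test had little or no chance of detecting a benefit. A significant result at a visit held before the first session would reflect chance, not ESWT. Either way, the result carrying the primary label would not address the stated aim.

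**Working it through.** **1. Timeline.** Both dates are counted from surgery.

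- First session: month 6. Primary assessment: month 6. Difference: 6 − 6 = 0 months.
- Four sessions one week apart put the last session 3 weeks after the first. Taking month 6 as week 26, the sessions fall at weeks 26, 27, 28 and 29.
- Next scheduled assessment: 1 year, week 52. Time since the fourth session: 52 − 29 = 23 weeks.

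No section counts the 6 months from ESWT, and none places the 6-month visit after the sessions.

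**2. The plan's own sample size.** The standardised difference is 6.5 / 6.9 = 0.942, and its square is 0.887. The normal approximation is n per group = 2(z_α + z_β)² / 0.887.

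- One-sided 5%: 2(1.645 + 0.842)² / 0.887 = 13.9, so 14. The exact t calculation gives 15, with power 80.8%.
- Two-sided 5%: 2(1.960 + 0.842)² / 0.887 = 17.7, so 18. The exact t calculation gives 19, with power 80.7%.
- Loss of 20%: 30 / 0.8 = 37.5, so 38.

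The stated 15 and 38 reproduce, but only with a one-sided test. The article does not state sidedness. That is a separate matter; it enters here only as the reason for showing both 15 and 19 per group below (38 / 2 = 19 with no loss).

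**3. Chance of a significant result at month 6.** Suppose a fraction f of the 6.5-point effect is present at the visit. For a two-sided t test the noncentrality is f × 6.5 / (6.9 × √(2/n)), which at f = 1 is 2.58 for n = 15 and 2.90 for n = 19. The protocol does not give f, so the values 0.25 and 0.50 are assumptions that show a range.

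| Situation at the 6-month visit | f | 15 per group | 19 per group |
|---|---|---|---|
| Before the first session | 0 | 5% | 5% |
| During the course (assumed) | 0.25 | 9.6% | 10.9% |
| During the course (assumed) | 0.50 | 23.8% | 29.3% |
| Full planned effect, for reference | 1 | 70.2% | 80.7% |

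With f = 0 the rejection rate equals the significance level whatever the sample size.

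**The case against.** **The order within month 6 is not given.** The article states no visit window and does not say whether assessment or first session comes first. The SPIRIT figure, said to show the schedule in detail, is not in the text at hand. A reader might infer that the true difference is zero by design and that the chance of significance is 5% however well ESWT works. That holds only if the visit precedes the first session, which is the nominal reading but is not stated. This part of the objection stands, and it is why the 10% to 29% range is shown. It does not rescue the time point, because a visit during the course still measures incomplete treatment.

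**The later visits are kept.** This also stands. The 1-year and 2-year comparisons are planned, so data from after treatment will exist and the trial can still address its question. The fault lies in which comparison is called primary.

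**The 80% power is not tied to month 6.** The Sample size section names VISA-A but no time point. Setting 5%, or 10% to 29%, against 80% assumes that the power was meant for the primary time point. That is the usual intention, but the article does not say so.

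**Multiplicity.** From the words about 1 year and 2 years, a reader might infer three co-primary tests with an inflated error rate, or an ordered sequence in which a null 6-month test blocks the later ones. The article states neither. It names one primary point and lists later analyses in time order, and multiplicity rules may stand in an analysis plan that is not shown. The timing conflict does not depend on either reading.

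**An analysis plan could settle it.** The protocol fixes the time point explicitly. A plan that followed it would inherit the problem, and one that departed from it would contradict the protocol.

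**Conclusion.** The point holds. By its own dates, the protocol places the primary efficacy assessment at the nominal start of the randomised treatment, with the course ending about 3 weeks later. The abstract and Procedures agree on the start of treatment, so this is not a single slip there.

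If the visit precedes the first session, the expected difference is 0 and the chance of a significant result is about 5%. If it falls during the course, two-sided power is about 10% to 29%, assuming that 25% to 50% of the 6.5-point effect is present, the SD is 6.9, and 15 to 19 per group are analysed. Both are far below the planned 80%.

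The documents do not support the stronger conclusion that the trial as a whole cannot detect an effect of ESWT, because later comparisons are planned. Nor do they show whether the slip lies in the choice of time point or in the origin from which the 6 months are counted.

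**What to change.** - **Reconcile** the treatment timing in the abstract and Procedures with the time point in Statistical analysis. If the 6 months were meant to run from another origin, say so.
- **Name one primary VISA-A time point after the randomised course.** The 1-year visit is the first scheduled one that qualifies, about 23 weeks after the fourth session. The 2-year comparison can then be secondary.
- **State how the 6-month assessment is ordered relative to the first session.** If it comes before, treat it as the pre-treatment value and not as the primary efficacy outcome.
- **State which time point the sample size refers to.** Naming 1 year does not by itself secure 80% power: if the 6.5-point difference applies there, a two-sided test has 70.2% with 15 per group and 80.7% with 19.

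**Cost.** No new visits and no change to the treatment schedule are needed. It is nevertheless a change of primary time point in a running trial. The Trial status section gives October 2018 as the start of recruitment and October 2021 as its expected end, and the article appeared in November 2022, so some 6-month data have probably been collected. The amendment should therefore be dated and justified without sight of outcome data by arm.

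### The group comparison is an unadjusted two-sample test, although an earlier VISA-A score is collected on every patient; adjusting for it would probably recover precision that a 38-patient trial needs

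*Protocol article*

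**What the plan says.** The Sample size section states: "The primary outcome of this study is the VISA-A score". Its inputs are a "minimum clinically important difference (MCID) of 6.5 points for the VISA-A" and a source that "indicates an expected standard deviation (SD) of 6.9 points". From these it concludes that "at a level of 5% significance and the most likely scenario for 80% power, 15 patients per group will be needed", and then: "Assuming a margin of 20% loss of primary outcome data, we propose to recruit a minimum of 38 patients in total".

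The Statistical analysis section fixes the method: "Group comparison will be statistically analyzed by either" Student's t test or the Mann-Whitney U test, "depending on whether the data is normally distributed". It names no covariate, change score or repeated-measures model. It makes 6 months after surgery the first point for efficacy, followed by 1 and 2 years.

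Under Procedures, VISA-A and the other scores are taken once a patient is included, before coblation. Then: "All the outcome measurements will be assessed again at 6 months, 1 year, and 2 years after the surgical procedure". ESWT or sham also starts at 6 months and runs for four weekly sessions.

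**The concern.** The best predictor of a patient's later VISA-A score is likely to be that patient's earlier VISA-A score, and the protocol already collects it. A two-sample test on the follow-up score leaves the between-patient variation that the earlier score explains in the error term. It also leaves any chance imbalance between two small arms in the estimate. With about 15 evaluable patients per arm there is little precision to spare.

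The plan also lets the observed data decide whether the primary test compares means or ranks. The sample size is built on a mean difference in VISA-A points, so the primary test should address that quantity whatever a normality check shows.

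**Working it through.** **Inputs.** From the Sample size section: difference δ = 6.5, SD σ = 6.9, significance 5%, power 80%, 15 per arm, 20% loss, 38 in total. Not in the documents: sidedness (taken as two-sided below) and the correlation ρ between the earlier and later VISA-A (shown over a range).

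**1. The protocol's own figure.** The t test sample size for 80% power is 14.66 per arm one-sided, which rounds to 15, and 18.70 two-sided, which rounds to 19. Allowing for loss, 15/(1 − 0.2) = 18.75, so 19 per arm and 38 in total. The stated 15 and 38 therefore reproduce with a one-sided t test. Two-sided, 19/(1 − 0.2) = 23.75, so 24 per arm and 48 in total.

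**2. The planned unadjusted test, 15 per arm.**
- SE = σ√(2/n) = 6.9 × √(2/15) = 2.52 points.
- Noncentrality = 6.5/2.52 = 2.58 on 28 df.
- Two-sided power = 70.2%.

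**3. ANCOVA on an earlier VISA-A score, 15 per arm.**
- Residual SD = σ√(1 − ρ²).
- Chance covariate imbalance inflates the variance on average by 1 + 1/(2n − 4) = 1 + 1/26 = 1.0385.
- SE = σ√(1 − ρ²) × √(2/15) × √1.0385, on 2n − 3 = 27 df.
- Worked case, ρ = 0.5: residual SD = 6.9 × √0.75 = 5.98; SE = 5.98 × 0.3651 × 1.0190 = 2.22; noncentrality = 6.5/2.224 = 2.92; power = 80.5%.

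| ρ (assumed) | SE, points | Two-sided power |
|---|---|---|
| unadjusted test | 2.52 | 70.2% |
| 0 | 2.57 | 68.5% |
| 0.2 | 2.52 | 70.2% |
| 0.3 | 2.45 | 72.5% |
| 0.5 | 2.22 | 80.5% |
| 0.6 | 2.05 | 86.2% |
| 0.7 | 1.83 | 92.7% |

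Without the imbalance term, power at ρ = 0.3, 0.5, 0.6 and 0.7 would be 74.1%, 81.9%, 87.5% and 93.6%. The table uses the more cautious figures. The break-even correlation is about 0.2.

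**4. The choice of test.** The procedure was simulated with normal data, 15 per arm and 6,000 runs per setting. The protocol names no normality check, so Shapiro-Wilk on each arm was assumed, with Mann-Whitney used if either arm rejected. Type I error was 4.9% to 5.3% and power 69% to 71%, whatever ρ was. ANCOVA on the same data had 80% power at ρ = 0.5 and 93% at ρ = 0.7. The shortfall comes from not adjusting, not from the switch.

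**5. Which earlier score.** The pre-surgery score precedes every follow-up visit, so it can be the covariate at any of them. The 6-month score cannot be both the outcome at the protocol's first efficacy point and its own covariate, so it is available only for 1 and 2 years. Procedures places the 6-month assessment and the start of ESWT at the same nominal time without giving their order.

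**The case against.** An unadjusted two-sample test in a randomised trial is unbiased and valid, so the point concerns efficiency, and its size rests on a correlation nobody has stated. That stands: at ρ = 0.2 nothing is gained, and at 0.3 only about 2 points. The 70% baseline also depends on a two-sided test and exactly 15 evaluable per arm. One-sided power at 15 is 80.8%, and if all 19 per arm were evaluable, unadjusted two-sided power would be 80.7%. Moreover, 38 is a stated minimum.

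It can also be said that the article does not specify raw or change scores, and that a change-score test would use the baseline. It would, but its variance is 2(1 − ρ)σ² against (1 − ρ²)σ² for ANCOVA. It beats the raw comparison only when ρ exceeds 0.5, and since 1 + ρ cannot exceed 2 it never has the smaller residual variance. Nor is this a detail left to an analysis plan: the article itself fixes the tests.

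Three stronger readings are tempting and are not supported:
- **The switch inflates type I error or costs power.** The simulation above shows neither with normal data. With a skewed distribution (gamma, shape 4, 15 per arm, 4,000 runs), type I error was 5.2% and power 75%, against 72% for always using the t test.
- **A Mann-Whitney result would leave only a p value.** The protocol commits to means and SDs for all continuous outcomes, so a raw difference could still be set against 6.5 points.
- **The 6-month score is a ready-made pre-ESWT baseline.** The order of assessment and treatment is not stated, and the Statistical analysis section makes 6 months the primary efficacy point.

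**Conclusion.** The plan fixes a valid but inefficient comparison when a better one is available from data already scheduled. At δ = 6.5, σ = 6.9, two-sided 5% and 15 evaluable per arm, adjusting for an earlier VISA-A score moves power from 70% to about 73% if ρ is 0.3, 80% if 0.5 and 93% if 0.7. It makes no difference at 0.2 and costs under 2 points at 0. The size of the gain is unknown because ρ is unknown, but the possible loss is small and the possible gain large, so adjustment is the better choice to fix in advance. The case against the data-dependent test is only that the primary analysis should keep one target, the mean difference in VISA-A points. No error-rate fault is claimed.

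**What to change.** Pre-specify, before unblinding, ANCOVA of VISA-A on treatment with an earlier VISA-A score as covariate, or a mixed model over the visits with that covariate. Report the adjusted mean difference with its 95% CI against 6.5 points. Make this the primary analysis in place of the choice between t test and Mann-Whitney, and keep the rank test as a sensitivity analysis.

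State which score is the covariate. The pre-surgery score can be used at every time point. Use the 6-month score only for the 1-year and 2-year analyses, and only after two things are settled: Procedures and Statistical analysis are reconciled on the primary time point, and the 6-month assessment is confirmed to precede ESWT.

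Adjusting for the pre-surgery score changes only the analysis wording and costs one degree of freedom, with no extra patients, visits or measurements. Using the 6-month score depends on the primary time point, which is a larger decision than wording.

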### Patient and public involvement

Neither patients nor the public was involved in the design of the study, including conceiving the research questions and deciding the outcomes. However, all participants will be asked whether they would like to receive a copy of the trial results at the time of consent. Once completed the trial, a copy of the personal results will be emailed to participants who said yes. Also, the burden of the intervention will be assessed by participants themselves using a questionnaire [39, 40].

## Discussion

Nonoperative management is the first line of treatment for IAT, though the most effective standard procedure is controversially debated [41]. However, conservative therapy is a time-consuming procedure, and approximately a quarter to half of all patients do not respond to it [20, 42]. Thus, as a minimally invasive operation, percutaneous radiofrequency coblation has been brought into attention. This technique allows patients to hasten their resolution of pain and shorten their return to activity [26, 43] though there is insufficient evidence to prove its clinical efficacy of Achilles tendinopathy, especially when the BMI of the patient is relatively high [33]. On the other hand, isolated ESWT has been reported as an alternative option for IAT by extensive studies [15, 44]. Rompe et al. [45] have showed ESWT is more beneficial in combination with eccentric exercises in non-insertional tendinopathy. Then we intend to seek for a combination method for insertional tendinopathy as well. This study protocol describes the randomized controlled trial directly comparing the effectiveness of percutaneous radiofrequency coblation associated with ESWT and isolated percutaneous radiofrequency coblation.

To our best knowledge, most studies used isolated VISA-A score as the primary outcome measurement for the prognosis of Achilles tendinopathy [46, 47] because it is the validated assessment for this quite frequent disorder. However, at the same time, there are few radiographic descriptions of the Achilles tendon. Therefore, we introduce MRI UTE-T2* as our secondary outcome measurement to monitor the status of Achilles tendon and to see the correlations with clinical scores besides the comparison of the effectiveness on function and pain between 2 interventions, which could be our secondary aim.

In conclusion, this randomized, double-blinded, parallel-group clinical trial aims to investigate if radiofrequency coblation associated with ESWT can provide more encouraging imaging findings and functional and clinical outcomes regarding the treatment of the IAT compared to the single radiofrequency coblation treatment.

